#### Module 1: identify and tackle avoidance behavior

During this module the patient will learn to identify his/her avoidance behavior in daily life that has an impact on anxiety and depressive symptoms. These symptoms lead to either an increase of anxiety and thereby an increase of avoidance behavior or to less interest while undertaking the activities and less satisfaction. This vicious circle and the importance of breaking this pattern will be explained to the patient. This will be done by identifying what specific situations are avoided by the patient in daily life and by eventually replacing avoidance behavior by alternative behavior. In case of depression the therapist will stimulate behavioral change by helping patients to become more active by increasing mood independent potential pleasurable (reinforcing) activities in their lives (behavior activation) [19-21]. The ultimate goal is to teach patients to actively react to difficult or painful situations or emotions instead of avoiding them (becoming pro-active rather than reactive to mood swings) [19].

#### Module 2: illness-history writing assignment

IBD patients often have a long illness history. This may consist of unprocessed negative experiences. For emotional processing of these negative experiences it is important that these experiences are identified and processed. Therefore, the patient will be asked to write about the most painful memories of his/her illness history in order to stimulate the processing of that memory [22,23]. The most painful memories are usually the ones that are being avoided or suppressed. The patient will write as detailed as possible about the most painful images (e.g. physician’s face, surgeon, hospital appliances, intensive care unit), thoughts (e.g. it is my fault, I am going to die) and emotions (e.g. embarrassment, feeling dirty and helpless). In a subsequent session the patient will read the most painful pieces of the assignment out loud. In this way the patient will be exposed to the most painful images, cognitions and emotions. Additionally, the therapist will identify the dysfunctional cognitions and attitudes of the patient.

#### Module 3: imagery with rescripting

The patient may experience intruding traumatic illness-related memories (flashbacks). During imagery with rescripting the patient will re-experience and rewrite the most painful memories in his/her imagination. Together the patient and therapist will compose a hierarchy of fearful situations and choose one or more of the most traumatic experiences to work through during imagery with rescripting. The patient will be asked to imagine the traumatic situation as lively as possible. After sufficient exposure the experience must be “re-written” following three phases. This will be done by returning to the negative experience in the patient’s imagination and altering it into satisfying new feelings, helpful attitudes and corrective experiences (e.g. support or presence of partner/parent) [24-26].

#### Module 4: cognitive therapy

In order to decrease emotions such as fear, sadness and anger cognitive therapy focuses on automatic negative thoughts and underlying dysfunctional attitudes that lead to these emotions. The cognitive model states that attitudes develop during childhood and are based on particular life events and/or views of significant others (e.g. parents or teachers) [12,27]. This determines one’s interpretation of one self, others and the world. For instance, an early experience such as being bullied at school can trigger the activation of dysfunctional attitudes such as ‘I am worthless’. Later in life, when a critical event, such as the diagnosis of IBD takes place, the dysfunctional attitudes may be activated. These, in turn, activate negative or anxious automatic thoughts such as ‘Now that I am sick, I am worthless’. These negative automatic thoughts can in turn cause anxiety and depressive symptoms. The ultimate aim of this module is to identify, challenge and alter dysfunctional attitudes of patients into helpful ones that fit in the current circumstances [28].

#### Module 5: relapse prevention plan

During the last two sessions the therapist will work with the patient on the steps that can be undertaken in order to prevent relapse. The patient will learn to signal potential relapse (e.g. symptoms like worrying, avoiding activities) and to develop prevention strategies. For instance, the patient might make use of tools such as flash cards with helpful attitudes, in order not to spiral back into the old dysfunctional ones [28].

### Sample size

We will consider a difference of 0.5 standard deviation, which is equal to a moderate effect size [29], clinically relevant. For calculating the required difference on the Inflammatory Bowel Disease Questionnaire (IBDQ), we will use the data from a study by McColl et al [30] among 111 IBD patients. The mean IBDQ score was 182 and the standard deviation was 59. A 0.5 standard deviation thus equals approximately 30 points on a scale ranging from 32 to 224. With an effect size of 0.5 standard deviation, an alpha level of 0.05, and a power of 80%, at least 34 patients in both the experimental condition and the waiting list control condition are needed. Given a potential attrition rate of 10%, we will include 40 patients in each condition.

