A recent meta-analysis of 21 studies was conducted that evaluated the effect of psychological treatment on quality of life, emotional status and disease activity in IBD [15]. The psychological treatments included psycho-education as intervention (10 studies), stress management (3 studies), psychotherapy (6 studies) and other non-specific techniques like a support group (2 studies). Of all included studies only 6 studies evaluated the effect of a multi modular approach including IBD psycho-education (4 of them included CBT techniques). Overall, no significant effects of psychological interventions were found on improving health related quality of life, emotional problems and disease activity. All studies included suffered from various methodological shortcomings such as small sample sizes and non-random sampling. Moreover, all but one study included patients who did not have elevated levels of distress, thereby diluting the treatment effect. Patients in these studies seemed relatively healthy, so perhaps there was no room for improvement. Inclusion of patients with higher anxiety and depressive symptoms may have resulted in more positive effects. Only one study selected patients based on HADS anxiety levels [16]. Given these methodological shortcomings and the many multi-component interventions, it is still unclear what the effects of a specific CBT are. We have, therefore, developed a CBT that is specifically designed for patients with IBD who have a poor quality of life, thereby targeting a patient group that is most burdened by the illness.

We will examine the effectiveness of CBT in this study by using a randomized waiting-list control design, including a sufficiently large number of patients who have elevated levels of mental distress. This paper contains a detailed description of the design of this randomized controlled trial investigating the effectiveness of CBT specifically designed for IBD patients.

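### The stated inputs (0.5 SD, alpha 0.05, 80% power) do not give 34 per condition for a two-arm comparison; they give 64, or 51 one-sided

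*Protocol article*

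**What the plan says.** The Sample size section of the protocol article treats half a standard deviation as clinically relevant. It takes the IBDQ spread from an external study of 111 IBD patients: "The mean IBDQ score was 182 and the standard deviation was 59". It then translates the target into points: "A 0.5 standard deviation thus equals approximately 30 points on a scale ranging from 32 to 224". The inputs are given as "With an effect size of 0.5 standard deviation, an alpha level of 0.05, and a power of 80" per cent, and the result is that "at least 34 patients in both the experimental condition and the waiting list control condition are needed". The attrition step follows: "Given a potential attrition rate of 10%, we will include 40 patients in each condition".

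The section gives no formula, no sidedness, and no correlation between baseline and follow-up IBDQ.

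The Statistical analysis section sets the primary comparison between the experimental and waiting-list conditions. It describes analyses of covariance for improvement and a factorial analysis of variance with condition as between-factor and assessments as within-factor. It adds the stratification variables as covariates. It does not say in so many words that baseline IBDQ is a covariate.

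**The concern.** The primary question compares two separately randomised groups. Half an SD is a familiar target, and the two-group size for 80% power at two-sided 0.05 is a little over 60 per group. A figure of 34 per group is close to half of that, and nothing printed in the section accounts for the difference.

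This is the only power statement for the primary outcome. If it is wrong, readers will believe the trial can reliably detect 0.5 SD when it may not. A non-significant result could then be read as evidence that the adapted CBT does not work, when the trial may simply have been too small for the effect it called relevant.

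**Working it through.** **Inputs from the Sample size section.** Standardised difference d = 0.5; alpha 0.05; power 80%; SD 59; stated need 34 per condition; 40 enrolled per condition; attrition 10%, so 40 × 0.9 = 36 evaluable. Sidedness is not stated: two-sided is assumed, and one-sided is also shown. Allocation is 40 to 40 (Abstract).

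**Step 1: looking for the stated 34.** Power and sample size use the noncentral t distribution.

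| Test at d = 0.5, alpha 0.05, 80% power | n solved | n needed |
|---|---|---|
| Two independent arms, two-sided | 63.8 | 64 per arm |
| Two independent arms, one-sided | 50.2 | 51 per arm |
| One-sample or paired, two-sided | 33.4 | 34 |

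The normal approximation for two arms, n = 2(1.96 + 0.84)²/0.5², gives 63 per arm. Using 30/59 = 0.508 in place of 0.5 gives 61. Neither approaches 34. The one-sample or paired test matches: its power is 79.5% at n = 33 and 80.8% at n = 34.

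**Step 2: two-arm power without credit for baseline.** The noncentrality parameter is d√(n/2), with 2n − 2 degrees of freedom.

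| n per arm | Power, two-sided | Power, one-sided | Difference with 80% power, two-sided |
|---|---|---|---|
| 34 | 53% | 65% | 0.69 SD |
| 36 | 55% | 68% | 0.67 SD |
| 40 | 60% | 72% | 0.63 SD |

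If the SD is 59, the detectable differences at 34 and 36 per arm are 0.690 × 59 = 40.7 and 0.670 × 59 = 39.5 points. The section's target is about 30 points.

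**Step 3: two-arm power with baseline used.** Let r be the correlation between baseline and follow-up IBDQ. The document gives no value, so every r below is an assumption. Equal variances at both times are also assumed.

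- Baseline-adjusted ANCOVA: effective d = 0.5/√(1 − r²).
- Change score, or condition-by-assessment test with two time points: effective d = 0.5/√(2(1 − r)).

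| r | ANCOVA, 34 per arm | ANCOVA, 36 per arm | Change score, 36 per arm |
|---|---|---|---|
| 0.5 | 65% | 68% | 55% |
| 0.6 | 72% | 74% | 65% |
| 0.7 | 81% | 83% | 77% |

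ANCOVA reaches 80% when 0.5/√(1 − r²) equals the detectable difference of Step 2. At 34 per arm, r = √(1 − (0.5/0.690)²) = 0.69. At 36 per arm, r = √(1 − (0.5/0.670)²) = 0.67. The change-score test at 36 per arm needs r = 1 − (0.5/0.670)²/2 = 0.72.

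**Step 4: the attrition allowance.** 34/0.9 = 37.8, so 38 would suffice to retain 34. Enrolling 40 adds a small margin and does not close the gap to 64.

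**The case against.** The strongest reply is that 53% to 55% describes an unadjusted comparison of follow-up scores, which is not what the Statistical analysis section plans. That section speaks of covariance analysis of improvement and a within-factor for assessments, and the sentence on stratification variables adds to that model. It would be too narrow to read it as saying that only gender, center and disease type are adjusted for. This stands. A reader might infer that the trial's true power is about 55% and that a real 0.5 SD effect would be missed nearly half the time. The document does not support that as a fact, because the power of the planned analysis depends on a correlation it does not state.

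Second, a reader might infer that the authors used a paired formula by mistake. The match is exact, but no formula is named, and a baseline-adjusted ANCOVA with r of about 0.69 leads to the same number. The origin of 34 remains unknown. A fuller protocol might state a correlation, but the sentence as printed would still not follow from its own inputs.

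Third, the translation into points relies on an SD of 59 from another sample, whereas this trial selects on low mental health scores. If the SD here were smaller, power for 30 points would be higher: at 36 per arm without baseline, 57% at SD 59, 71% at SD 50 and 83% at SD 43 (the last two SDs are assumptions). This limits the figures in points. It does not affect the result in SD units, which is how the section defines its target.

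**Conclusion.** The calculation is wrong as written and must be corrected. The printed inputs give 64 per arm two-sided or 51 one-sided for two independent arms, not 34, and this conclusion needs no view on how 34 arose.

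What the trial can detect is less certain. With no credit for baseline and a two-sided test, 36 evaluable patients per arm give 55% power for 0.5 SD. With baseline-adjusted ANCOVA the claimed 80% is attainable, but only if the correlation is about 0.67 or higher at 36 per arm (0.69 at 34). A condition-by-assessment test on two time points needs more, about 0.72 at 36 per arm, and at r = 0.5 gains nothing over the follow-up-only comparison. So 80% power for 0.5 SD is possible but unsupported by anything the document states.

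**What to change.** Keep 40 per condition and rewrite the paragraph:

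- Remove the claim that 34 per arm gives 80% power for 0.5 SD.
- State that baseline IBDQ is a covariate in the primary ANCOVA, alongside the stratification variables, and that the test is two-sided if that is intended.
- Base the power statement on that ANCOVA, with a stated correlation and its justification.
- Show power at 36 evaluable per arm for r = 0.5, 0.6 and 0.7 (about 68%, 74% and 83%), with the no-baseline figure as the lower bound for the ANCOVA: 55% for 0.5 SD, or 80% for 0.67 SD.

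This costs one paragraph and no extra patients. The downside is a less favourable power statement. If 80% power for 0.5 SD must hold without relying on baseline, the alternative is 64 evaluable per arm, which at 10% attrition is 64/0.9 = 71.1, or 72 enrolled per arm.

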#### Feasibility

Approximately 1600 IBD patients are treated at the AMC on a yearly basis. Given the fact that patients may be eligible regardless of time since diagnosis, the number of patients to be included in only one center is feasible. However, to enhance recruitment in a relatively short time period and promote future dissemination we will recruit patients in three additional medical centers (i.e. Slotervaart-hospital, Flevo-hospital and VUmc). Two of the four participating centers are academical medical centers (i.e. AMC and VUmc). Based on the literature [31], we expect 10-20% of the IBD patients to have a score below the cut-off point and be eligible for the study.

### Inclusion criteria and exclusion criteria

Inclusion criteria will be: (1) a diagnosis of Crohn’s disease or ulcerative colitis; (2) age above 18; (3) a score of 23 or lower on the mental health scale of the SF-36; (4) physically and mentally able to attend eight weekly sessions; and (5) sufficient command of Dutch. Exclusion criteria will be: (1) current psychological treatment; and (2) known psychiatric disorders that may complicate treatment (current substance dependence or abuse, current psychosis).

### Recruitment and informed consent

Patients who have a score of 23 or lower on the mental health subscale will be eligible for the study. The mental health subscale consists of 5 items that require a response on a 6-point scale (range 5–30). The cut-off score of 23 is chosen as scores of 23 or lower are found indicative (with a high level of sensitivity and specificity) of depression and anxiety in primary care patients [17]. If this step is ignored a failure of a positive effect may be contributed to high baseline scores and lack of room for further improvement [15]. Consequently, the researcher will contact patients by telephone to ask whether they are willing to participate and to check whether informed consent is received. If the participant meets all inclusion criteria and is willing to provide informed consent, an appointment will be made to administer the SCID-I by telephone.

The SCID-I will be used as a screening measurement before randomisation.

### Outcome measures

*Sociodemographic assessment* will include age, gender, educational level, employment status, marital status, ethnicity, and treatment center.

*Clinical physical data* will be completed by the treating gastroenterologist, and will include type of disease (Crohn’s disease and ulcerative colitis), date of onset of disease, having a colostomy, and number of operations. Finally, the biological markers of disease activity (e.g. C-reactive protein (CRP)) of each patient attending the outpatient department will be registered in an electronic database. Additionally disease activity will be measured using the following illness specific questionnaires: the Harvey Bradshaw index (P-HBI) for patients with Crohn’s disease and Simple Clinical Colitis Activity Index (P-SCCAI) for patients with ulcerative colitis. These patient-based questionnaires were specially developed for the current study [32]. The original SCCAI has good validity and reliability [33].

***Primary outcome measures ***the Inflammatory Bowel Disease Questionnaire (IBDQ) will be used to assess the primary outcome of the intervention [34]. The IBDQ measures health-related quality of life and consists of 32 items assessing four dimensions: bowel symptoms, systemic symptoms, emotional functioning, and social functioning. In addition to these four subscale scores, a total score can be calculated [20]. The IBDQ has good construct and criterion validity, test-retest reliability and high internal consistency [35].

***Secondary outcome measures ***the MOS SF-36 is a 36-item questionnaire assessing generic health-related quality of life or health status [36]. The items can be aggregated into a Physical Component Summary score and a Mental Component Summary score. The SF-36 has high internal consistency and good reliability and discriminant validity [37].

The Hospital Anxiety and Depression Scale (HADS) assesses the possible presence of anxiety and depressive states [38,39]. The HADS is considered to be unbiased by the presence of somatic illness and is found to be reliable and valid [40]. It consists of two sub-scales, anxiety and depression, both containing seven items. The CES-D scale (The Center for Epidemiologic Studies Depression Scale) is a short self-report scale designed to measure depressive symptomatology in the general population. The CES-D has high internal consistency, satisfactory test-retest reliability and excellent concurrent validity [41].

***Mediation variables ***The Illness Perception Questionnaire-Revised (IPQ-R) assesses illness-related cognitions. The 48 items measure seven dimensions: timeline acute/chronic, timeline cyclical, consequences, personal control, treatment control, illness coherence and emotional representations. The IPQ-R has good internal and test-retest reliability and predictive and discriminant validity [42].

The 40-item Dysfunctional Attitude Scale (DAS) measures dysfunctional attitudes, including excessive and rigid beliefs [43]. The DAS has good psychometric properties regarding reliability, internal consistency and convergent construct validity [44].

The Utrechtse Coping Lijst (UCL) assesses general coping behavior in problem situations [45,46]. The subscales ‘problem-solving’ (7 items) and ‘avoidance’ (8 items) will be used. The UCL has good test-retest reliability, construct and predictive validity [47].

All standard self-report questionnaires fulfill the following selection criteria. They: (a) are relatively brief, (b) have sufficient breadth of coverage, (c) are widely used, and (d) yield adequate to high levels of reliability and validity.

An overview of the questionnaires at the different time points for the experimental and waiting-list control conditions is provided (see Table 1).

### Withdrawal

Subjects can withdraw from the study at any time for any reason if they wish to do so without any consequences. Nevertheless, we will ask those who withdraw from CBT treatment if they are willing to complete the web-based questionnaires at the respective time intervals.

#### Safety monitoring and reporting

The study will be conducted according to the principles of the Declaration of Helsinki and in accordance with the Medical Research Involving Human Subjects Act (WMO).

The Medical Ethical Committee (MEC) of the AMC offers exemption from participants insurance.

In general there will be few if any risks associated with the research in question. Since there is no indication and no evidence that the intervention might be harmful to patients, we will not anticipate premature termination of the study. Clearly, each individual patient has the right to withdraw from the study at any time he/she wishes.

Suspected serious adverse events will be recorded and reported to the MEC of the AMC.

### Statistical analysis

Analyses of covariance will be conducted to determine the extent to which treated patients (experimental condition) show more improvement on the primary and secondary outcome variables compared to patients in the waiting-list control condition. A two-way factorial analysis of variance with the between-factor condition (experimental condition versus waiting list control condition) and the within-factor assessments will be used. Moreover, stratification variables, i.e. gender, treatment center and disease type will be included as covariates in the analyses (ANCOVA).

Additionally, the data of experimental and the waiting-list control condition will be pooled, to measure the overall effect of treatment. Before the two groups will be pooled, we will examine whether there is a difference in effect for the experimental versus the waiting-list control condition (Delta T_follow-up after CBT_-T_baseline before CBT_). In case differences emerge, this will be stratified reported.

For therapy effects, data will be analysed on an intention to treat (ITT) as well as treatment completer basis. The completers sample will include patients who attend at least 5 CBT sessions.

To express the magnitude of the effects, mean gain scores on the outcome measures will be standardized to Cohen’s *d*, representing the number of standard deviations separating the two means. Point estimates and 95% confidence intervals of *d* will be determined for the within and the between group effects. Between effect sizes will be calculated using the pooled standard deviation (of the baseline scores) and confidence intervals will be approximated from the central *t*-distribution.

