**Figure 1 F1:**
[figure not shown]
Flow chart study design.

The SCID-I will be administered by telephone, by psychologists who received a specific training for this.

All patients will then be asked to complete a set of questionnaires that assess the baseline primary and secondary outcomes via the web (see Table 1). If patients prefer paper and pencil completion, these questionnaires will be sent. After completion of the first baseline assessment, patients will be randomly assigned to the experimental or waiting-list control condition. Randomization will be stratified by gender, disease type and type of medical center (peripheral or academic) and will be performed by an independent employee at the Department of Clinical Epidemiology and Biostatistics of the AMC.

**Table 1 T1:** Overview assessment schedule

**Measure**	**Description**	**T**_**baseline**_	**T**_**follow-up after waiting/baseline before CBT**_	**T**_**mid-treatment**_	**T**_**follow-up after CBT**_
*Screening SCID*-*I*^*^	DSM-IV-TR				
	Axis I disorders				
*Primary Outcome*					
IBDQ^**^	Inflammatory Bowel Disease Questionnaire	E C	C	E C	E C
*Secondary Outcome*					
SF-36^**^	MOS 36-item Short-Form Health Survey	E C	C	E C	E C
HADS^**^	Hospital Anxiety and Depression Scale	E C	C	E C	E C
CES-D^**^	The Center for Epidemiologic Studies Depression Scale	E C	C	E C	E C
P-HBI^**^	Patient-based Harvey Bradshaw Index	E C	C	E C	E C
P-SCCAI^**^	Patient-based Simple Clinical Colitis Activity Index	E C	C	E C	E C
*Potential Mediators*					
DAS^**^	Dysfunctional Attitude Scale	E C	C	E C	E C
IPQ-R^**^	Illness Perception Questionnaire-Revised	E C	C	E C	E C
UCL^**^	Utrechtse Coping Lijst	E C	C	E C	E C

*Experimental Condition* (*E*) *and Waiting list Control Condition* (*C*).

^***^*Interview that is administered by telephone.*

^****^*Web-based questionnaire.*

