Participants assigned to the experimental condition will start treatment as soon as possible (maximum within 6 weeks). The second, mid-treatment assessment will take place four weeks following start of treatment and the third assessment one month following completion of treatment. Following the first baseline assessment, participants assigned to the waiting-list control condition will wait 3,5 months before they are treated with CBT. This period corresponds to the duration of the CBT intervention and follow-up assessment of the experimental group. After this 3,5 month waiting period the participants in the waiting-list control condition will be asked to complete a follow-up after waiting/baseline before CBT assessment before starting treatment. Analogous to the procedure in the experimental condition, the mid-treatment assessment will take place four weeks following start of treatment and the follow-up assessment one month following completion of treatment (see Table 1).

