### Cognitive behavioral treatment manual

The treatment will consist of eight weekly sessions, each lasting one hour. The first session will focus on the rationale of cognitive behavioral therapy, i.e. the influence of (irrational or dysfunctional) cognitions and attitudes on (restrictive) feelings and behaviors. Additionally, goal setting will be initiated. Since patients may have a wide diversity of psychiatric problems (i.e. PTSD, anxiety disorders and depression), the treatment manual will encompass five optional modules for the therapist that focus on each of these disorders (i.e. exposure based for anxiety and PTSD, behavioral activation for depression). The subsequent sessions (2–6) will target teaching the patient to identify and challenge dysfunctional cognitions and attitudes related to IBD. Each session will address specific illness-related cognitions. If possible, dysfunctional cognitions and attitudes will be replaced by helpful cognitions and attitudes. Clearly, some of the dysfunctional cognitions are realistic and reflect the limitations that the disease imposes. Such thoughts will be worked through and intervention will focus on acceptance of these disease limitations. Finally, in the last two sessions, the newly learned cognitions and attitudes will be consolidated using specific CBT techniques such as flashcards with helpful cognitions or attitudes. As customary within CBT, each session patients will be given homework. The CBT will be conducted by registered psychotherapists, specialized in cognitive behavioral therapy.

All treatment sessions will be audio-recorded and therapists will receive feedback over the first two CBT treatments to promote treatment integrity. Additionally, regular supervision will be provided.

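### The condition-by-assessments ANOVA does not name the one treated-versus-untreated contrast that the two assessment schedules allow, and it does not list baseline IBDQ as a covariate

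*Protocol article*

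**What the plan says.** The Statistical analysis section states the aim as whether "treated patients (experimental condition) show more improvement on the primary and secondary outcome variables compared to patients in the waiting-list control condition". It opens with analyses of covariance, then specifies a two-way factorial ANOVA in which "the between-factor condition (experimental condition versus waiting list control condition) and the within-factor assessments will be used". The levels of the within-factor are not listed. The covariates named are the stratification variables: gender, treatment center and disease type. Baseline IBDQ is not among them.

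Table 1 gives the schedule for the primary outcome over four columns (baseline, follow-up after waiting, mid-treatment, follow-up after CBT): "Inflammatory Bowel Disease Questionnaire E C C E C E C". The second column is filled for controls only.

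Methods and design gives the timing. For the experimental arm: "The second, mid-treatment assessment will take place four weeks following start of treatment and the third assessment one month following completion of treatment". For controls: "participants assigned to the waiting-list control condition will wait 3,5 months before they are treated with CBT". They complete one assessment at the end of the wait, before CBT. After that, "Analogous to the procedure in the experimental condition, the mid-treatment assessment will take place four weeks following start of treatment", with a follow-up one month after the end of their own CBT.

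**The concern.** A condition-by-assessment factorial needs the same within-factor levels in both arms. Here the arms have different schedules, and the same label means a different thing in each arm once treatment status and time since randomisation are considered. A model over all scheduled assessments has an empty cell. A model over the labels that both arms fill compares patients on or after CBT with other patients on or after CBT.

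The primary question is whether CBT improves IBDQ relative to waiting. If the confirmatory contrast is not fixed, the analyst must choose it later, and the choices differ widely in what they estimate. There is a second issue on the correct pair: with only the stratification factors as covariates, the condition-by-time test is a comparison of gain scores. That is less precise than adjusting for baseline whenever the baseline-outcome correlation is below 1.

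**Working it through.** **The plan's own figure.** The Sample size section gives 34 per arm for 0.5 SD, alpha 0.05 and 80% power. The two-group normal formula n = 2(1.960 + 0.842)²/0.5² gives 63 per arm two-sided (64 with the t distribution) and 50 one-sided. The figure of 34 is therefore not reproduced as a two-group comparison. It matches a paired two-sided t-test (33.4, rounded up), or a baseline-adjusted analysis with a correlation of about 0.68, which the article does not state. So the sample size section does not settle which contrast or model is meant. The power figures below use 36 per arm, which is 40 less the planned 10% attrition.

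**Step 1: treatment status by assessment (Table 1 and Methods and design).**

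| Assessment | Experimental | Control |
|---|---|---|
| Baseline | untreated | untreated |
| Follow-up after waiting | not taken | untreated |
| Mid-treatment | during CBT | during own CBT |
| Follow-up after CBT | after CBT | after own CBT |

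Controls have one untreated post-baseline assessment, at the end of the wait. The experimental mid-treatment assessment has no untreated counterpart on any reading. The only treated-versus-untreated pair is experimental follow-up after CBT against control follow-up after waiting.

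**Step 2: do these two line up in time?** Taking a month as 52/12 = 4.33 weeks and counting from assignment:
- Experimental, CBT started at once: 8 + 4.33 = 12.3 weeks.
- Experimental, CBT started at the 6-week limit: 6 + 8 + 4.33 = 18.3 weeks.
- Control: 3.5 × 4.33 = 15.2 weeks.

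The pair is aligned to within about 3 weeks either way.

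**Step 3: what each choice of levels would estimate.** Simulation with 20,000 runs per setting, 36 or 40 per arm. Assumptions that are not in the article: equal correlation r between assessments, r = 0.5 or 0.7, and a CBT effect of 0.25 SD at mid-treatment and 0.5 SD at follow-up in either arm once treated.

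| Levels used | Expected between-arm difference | Rejection rate |
|---|---|---|
| Shared labels (baseline, mid-treatment, follow-up after CBT) | 0 | about 5%, equal to alpha |
| Order of questionnaire (experimental 1–3 against control 1–3) | mixed | 18–29% |
| Aligned pair, each against baseline | 0.50 SD | 55–59% (r = 0.5); 77–81% (r = 0.7) |

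**Step 4: gain score against baseline adjustment on the aligned pair.** In SD units, the gain score has SD √(2(1 − r)) and the baseline-adjusted outcome has SD √(1 − r²). The two-sided two-sample t-test at 0.05, 36 per arm, gives:

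| r (assumed) | Gain SD | 0.5/SD | Power | ANCOVA SD | 0.5/SD | Power |
|---|---|---|---|---|---|---|
| 0.3 | 1.183 | 0.423 | 42% | 0.954 | 0.524 | 59% |
| 0.5 | 1.000 | 0.500 | 55% | 0.866 | 0.577 | 68% |
| 0.7 | 0.775 | 0.645 | 77% | 0.714 | 0.700 | 83% |

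The variance ratio is 2(1 − r)/(1 − r²) = 2/(1 + r), which is 1.33 at r = 0.5. The gain-score analysis would need a third more patients for the same precision.

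**The case against.** The strongest reply is that the article points to the right contrast. Methods and design says that the wait matches the length of CBT plus follow-up in the experimental arm. The control-only column is named both as a follow-up after waiting and as a baseline before CBT. The stated aim compares treated patients with waiting-list patients. The comparison of on-CBT gains between the arms appears separately, as a check before pooling, and would be redundant if the main ANOVA already made it. A condensed article may also leave exact model levels to a fuller document.

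Much of this stands. A reader might infer that the planned analysis compares treated with treated, so that the effect cancels. The text does not say this: cancellation follows only from matching assessments by label, and the passages above argue against that. A reader might also infer that the condition main effect would be the test, or that patients with a missing assessment would be dropped against the intention-to-treat basis. Neither is stated. The aim is framed as improvement, which is the interaction, and missing-data rules may lie in an analysis plan that is not shown.

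The objection does not remove the rest. The article does commit to a model, and that model cannot validly be run over the schedule in Table 1 without a restriction that it does not state. The only between-arm comparison with its time points written out is the pre-pooling check, not the primary one. The opening mention of analyses of covariance could cover baseline adjustment, but the covariates then listed are only the stratification factors.

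**Conclusion.** The point holds as a badly fixed primary analysis. It does not show that the trial will compare the wrong groups. The within-factor is undefined although the schedules differ between arms, and the single valid randomised contrast has to be inferred. On that contrast the full 0.5 SD is estimated and nothing cancels. The zero expectation and 5% rejection rate apply only if assessments are matched by label.

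The remedy also goes beyond naming the pair. With the covariates as listed, power for 0.5 SD at 36 per arm is about 55%, and it rises to about 68% with baseline adjustment, both at r = 0.5. Over r from 0.3 to 0.7 the figures are 42–77% and 59–83%. The correlation is an assumption, since the article gives none. The calculation also assumes equal variances at both assessments and ignores any gain from the stratification covariates.

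**What to change.** Replace the factorial ANOVA as the primary analysis with one contrast: IBDQ total at experimental follow-up after CBT versus control follow-up after waiting. Estimate it by ANCOVA, or an equivalent linear mixed model, adjusted for IBDQ at the first baseline and for gender, type of center and disease type, in all randomised patients as assigned. State that control assessments taken after the start of their own CBT enter only the within-group and pooled analyses, and that the experimental mid-treatment assessment is not part of the between-arm test. Apply the same contrast, each with its own baseline, to the secondary outcomes.

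The cost is a change to the analysis text before the data are examined. All the assessments needed are already scheduled in Table 1, so no visits, questionnaires or patients are added.
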